**Figure 1 figure1:**
[figure not shown]
Cone beam computed tomography images images showing condylar morphology measurements: (A) condylar length between ACo–PCo, (B) condylar width between MCo–LCo, and (C) condylar height from SCo to the sigmoid notch. ACo: anterior condyle point; PCo: posterior condyle point; MCo: medial condyle poles; LCo: lateral condyle poles: SCo: superior condyle point.

### Sample Size

The sample size for this investigation was determined based on the expected difference in continuous condylar morphometric measurements between groups. The entire sample size estimation procedure, including the full statistical formula and parameter assumptions, is described in Multimedia Appendix 1 [6,23]. On the basis of these predictions, at least 45 participants will be needed per group (chronic AN chewers and nonchewers).

### Statistical Methods

This study will compare chronic AN chewers and nonchewers by using random sample selection and strong statistical methods, including the Student 1-tailed *t* test, 1-way ANOVA, and chi-square test. SPSS (version 27.0; IBM Corp) and GraphPad Prism (version 7.0; GraphPad Software) will be used for data analysis, and the Nawaz et al formula will be applied to determine sample size [24]. To ensure scientific reliability, the analytical strategy was adapted from the study by Almashraqi et al [6].

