**Objective:**

This study aims to evaluate and compare condylar morphology in chronic AN chewers and nonchewers by using 3D imaging.

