**Results:**

On comparison of condylar morphology between chronic AN chewers and nonchewers by using cone beam computed tomography, statistical variations relevant to structural and pathological alterations such as osteophytes, surface flattening, and erosions are likely to occur.

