## Results

Only individuals fulfilling the inclusion and exclusion criteria will be considered as study subjects. This study is a registered, unfunded protocol study (CTRI/2025/06/088238) and is currently in the pre-recruitment phase. Participant enrollment and data collection are scheduled to be conducted from September 2025 to May 2027. As of the time of manuscript submission, no participants have been recruited and data analysis has not yet commenced. The primary outcome will evaluate condylar morphological changes associated with chronic areca nut (AN) chewing, while secondary outcomes will assess pathological alterations of the condyle, including osteophyte formation with subcortical sclerosis, articular surface flattening of the superior condylar surface with subcortical sclerosis, abnormal condylar shape, and surface erosion. The results are expected to provide insights into the functional impact of chronic AN chewing on the temporomandibular joint and may aid in early identification of pathological condylar changes. Study results are anticipated to be published after completion of data analysis in 2027.

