## Discussion

Chronic AN chewing has been extensively associated with oral mucosal lesions. However, its impact on the TMJ, particularly on condylar morphology, remains insufficiently studied using CBCT. Almashraqi et al [6] investigated CBCT findings in the TMJ of individuals with a history of chronic qat chewing (QC). They examined TMJ dimensions and osteoarthritic alterations on CBCT. According to the qualitative CBCT results, QC had substantially more osteoarthritic alterations than non qat chewers, including osteophyte, subcortical sclerosis, articular surface flatness, and subcortical cysts. Quantitative assessments of condylar dimensions showed no significant difference among both categories. Notably, the chewing side of individuals with QC displayed more alterations than the nonchewing side. The findings show that chewing qat has negative effects on the TMJ, primarily in the form of osteoarthritic alterations [6].

Liu et al [9] performed a study to investigate the relation between severe tooth wear caused by betel nut chewing and the development of TMD. Age, sex, and severely worn dentition due to betel nut chewing were significant factors contributing to the overall occurrence of TMD. Multivariable analysis revealed a significant, dose-dependent association between intra-articular TMD and badly worn dentition resulting from betel nut chewing, indicating a direct relationship between the severity of tooth wear and the likelihood of developing intra-articular TMD [9].

Al-koshab et al [22] investigated the morphology of the condyle and glenoid fossa by using CBCT in South-East Asians. Condylar length and roof of the glenoid fossa (RGF) thickness did not differ significantly by sex; however, male participants had significantly larger condylar volume, width, height, and joint gaps. While the mean left condylar height and RGF thickness were higher, the mean right TMJ condylar volume, width, and length were significantly higher when comparing the 2 TMJs. With the exception of condylar height, which is larger in Chinese participants, we could not find any significant differences between the 2 ethnic groups’ condylar measures and RGF thickness [22].

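### A one-tailed t test is named for comparing chewers with nonchewers, but the article states no direction for condylar length, width or height

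*Protocol article*

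**What the plan says.** The Statistical Methods section of the protocol article says that chewers and nonchewers will be compared "by using random sample selection and strong statistical methods, including the Student 1-tailed" t test. The list of tests in full is: "including the Student 1-tailed *t* test, 1-way ANOVA, and chi-square test". The section does not assign a test to an outcome or say which tail the t test will use. It adds: "To ensure scientific reliability, the analytical strategy was adapted from the study" of chronic qat chewers (reference 6).

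The aim, in the Abstract, is to "evaluate and compare condylar morphology in chronic AN chewers and nonchewers by using 3D imaging". The main Results section says: "The primary outcome will evaluate condylar morphological changes associated with chronic areca nut (AN) chewing"; pathological alterations are secondary. The one expectation offered, in the Results paragraph of the Abstract, is that "statistical variations relevant to structural and pathological alterations such as osteophytes, surface flattening, and erosions are likely to occur".

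The Study Procedure section defines three continuous measures: condylar length, width and height. The Sample Size section rests the 45 per group on an expected difference in continuous measurements and leaves the parameters to Multimedia Appendix 1.

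On the condylar dimensions in the qat study, the Discussion states: "Quantitative assessments of condylar dimensions showed no significant difference among both categories". It also says that qat chewers had substantially more osteoarthritic alterations.

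**The concern.** A one-tailed test is a valid 5% test only for a direction set before the data are seen. Here the test is fixed and the direction is not stated in the article. Neither the objective nor the primary outcome supplies one, and the closest earlier study gives no lead for the dimensions.

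Two things are at stake. If whichever mean turns out larger decides the tail, the false-positive rate for that measure is twice the nominal level. If a tail is fixed in advance and the true difference runs the other way, the test cannot declare it significant, however large it is. The choice also affects what 45 per group can detect.

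**Working it through.** **Is a direction stated for the measures a t test would compare?**

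| Place in the article | What it gives | Sign for length, width or height? |
|---|---|---|
| Abstract, Objective | evaluate and compare | no |
| Abstract, Results | variations in osteophytes, flattening and erosions expected | no |
| Introduction | tooth wear leads to structural adaptation of the condyle | no |
| Sample Size | an expected difference in continuous measures | no |
| Results (main) | morphological changes as primary outcome | no |
| Discussion, qat study | no significant difference in dimensions | no |

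The qat study's excess of osteoarthritic alterations could support a direction for the qualitative findings. Those are categorical, and of the listed tests the chi-square test suits them, not the t test.

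**Inputs.** 45 per group comes from the Sample Size section, so df = 45 + 45 − 2 = 88. Alpha and power are not in the article. Assumed: alpha 0.05 (also 0.025 and 0.01) and power 80% (also 90%). The stated 45 cannot be reproduced, because its parameters are in Multimedia Appendix 1, which is not at hand.

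**False-positive rate per measure.** The one-tailed critical value is t(0.95; 88) = 1.662 and the two-tailed value is t(0.975; 88) = 1.987.

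- Tail fixed in advance: P(T > 1.662) = 0.050. Simulation of 100,000 null trials gave 0.0502.
- Tail chosen after the means are seen: P(|T| > 1.662) = 2 × 0.050 = 0.100. The simulation gave 0.0998.
- At other levels, 0.025 becomes 0.050 and 0.01 becomes 0.02.

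The rate therefore lies between one and two times nominal. Results with |t| between 1.662 and 1.987 are significant only because of the tail.

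**What 45 per group can detect.** Power comes from the noncentral t distribution with df = 88 and noncentrality d × √(45/2), where d is the difference in SD units.

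- 80% power, one-sided 5%: d = 0.528.
- 80% power, two-sided 5%: d = 0.597.
- Two-sided power at d = 0.528: 0.698, about 70%.
- One-tailed test against a true difference of 0.597 SD in the opposite direction: power below 0.0001.

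The normal approximation agrees closely: (1.645 + 0.842) × √(2/45) = 0.524 one-sided and (1.960 + 0.842) × √(2/45) = 0.591 two-sided.

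**If 45 came from a one-sided 5% calculation.** Keeping the same effect and power with a two-sided test needs 58 per group at 80% power or 56 per group at 90%. Keeping 45 lowers two-sided power from 80% to about 70%, or from 90% to about 83%. If 45 came from a two-sided calculation, nothing changes.

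**The case against.** A one-tailed test with a direction set in advance keeps its level, and nothing in the article says the tail will follow the data. This stands: the doubling is a ceiling, not a property of the plan.

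A direction and a sidedness may also sit in Multimedia Appendix 1. That stands too. The point is limited to what the article states, although the test itself is fixed in the article, where a reader would look for its direction.

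The article does not label the t test as the main analysis, and Bias Mitigation plans multivariable adjustment, which could carry the main inference. This stands in part. Reading the t test as the primary comparison is an inference from the primary outcome and the continuous basis of the sample size.

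A non-significant result in qat chewers does not rule out a directional hypothesis for areca nut. True, but it does not supply one either.

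Some stronger readings are tempting and are not supported:

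- A reader might infer that the study's type I error is 10%. That needs a tail chosen after the data and a 5% level that the article does not state.
- A reader might infer that the qat study found no difference at all. The Discussion limits that result to dimensions and reports more osteoarthritic alterations.
- A reader might say that the plan's own mechanisms push the dimensions both ways, with osteophytes enlarging and erosion or flattening shrinking them. That is plausible, but the article does not say it.
- Listing ANOVA and chi-square beside a one-tailed t test is not a contradiction, since both are normally omnibus tests.

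**Conclusion.** The point holds in a limited form. The article fixes a one-tailed t test without a stated direction for the dimensions it would compare, and neither its objective, its primary outcome nor its account of the source study supplies one. This is a stated choice that is badly fixed, not a detail left to another document.

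At an assumed 5% level, the false-positive rate per measure is 5% if the tail is set beforehand and 10% if it follows the data. In the first case, a difference in the opposite direction cannot be declared significant; it could still be reported descriptively. Whether the sample-size statement is affected depends on the sidedness used in Multimedia Appendix 1, which cannot be judged from the article.

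**What to change.** In Statistical Methods, replace the one-tailed test with a two-sided Student t test, state its level (5% is assumed here), and report a 95% confidence interval for each difference in length, width and height.

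Then check which sidedness Multimedia Appendix 1 used. If it was one-sided at 5% with 80% power, keep 45 per group and restate power as about 70% for that effect, or give the detectable difference at 80% power as about 0.60 SD instead of 0.53 SD. If it was two-sided, leave the sample-size statement alone.

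The cost is a short wording change and, in the one-sided case only, a slightly less favourable power or detectable difference. The article says no participants had been recruited at submission and that analysis follows completion of enrolment and imaging, so the change should be made and dated before any group data are seen.

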### Reliability Assessment

A reliability plan has been included to ensure measurement accuracy. Two radiologists who had attended calibration sessions standardized landmark identification and measurement techniques. This will be according to the principles used in the study by Almashraqi et al [6]. They will assess all CBCT scans independently by using a standardized protocol. Intraobserver and interobserver reliability will be evaluated on 20% of randomly selected scans by using intraclass correlation coefficients, with values ≥0.80 considered acceptable. Any discrepancies will be reviewed and resolved by consensus to ensure consistent and reproducible measurements.

### Data Collection, Management, and Analysis

#### Plan of Data Collection

Patients who report to the Department of Oral Medicine and Radiology will have their AN chewing habit assessed. Following diagnosis, the patients will provide written informed consent and receive a comprehensive explanation of the intervention process. After consent has been obtained, CBCT will be used to analyze the AN chewer prospectively. This will create the following 2 distinct groups: AN chewers (45/90, 50%) and nonchewers (45/90, 50%), based on the patient’s habit history and comprehensive clinical examination. To improve transparency and reproducibility, the manuscript includes clearer and more organized reporting of the study design, participant recruitment, and flow. It also defines outcome measures. Additional details specify how CBCT imaging will be done, how clinical and habit-related data will be collected, and how all measurements will be recorded and analyzed. The procedures for radiologists, who were blinded to chewing status and attended calibration sessions, reliability testing, and statistical analysis, have also been described in more detail. This enhances methodological clarity and ensures that the study protocol is fully reproducible. All the results will be documented in a standardized tabular manner, as shown in Multimedia Appendix 2.

#### Data Collection and Retention

Proper counseling regarding the disease will increase the patient’s participation in the study.

#### Data Management

A master data sheet will be created to include the CBCT image data of the AN chewers and nonchewers, along with the difference in condylar morphology and pathological alterations in each group. All collected data will be assigned coded identifiers, and no personal information will be stored with the clinical or CBCT records. Digital files, including scan data and measurement sheets, will be stored on password-protected institutional servers. Access will be limited to authorized study investigators only. Data will be backed up regularly on secure, encrypted systems to prevent loss or unauthorized access. These measures ensure confidentiality, data integrity, and adherence to institutional ethical standards.

### Data Monitoring

Oversight of data accuracy, protocol compliance, and ethical adherence will be maintained by the Department of Oral Medicine and Radiology under the supervision of the guide and the IEC. No interim analyses or stopping guidelines are applicable to this observational study. Data will be analyzed only after completion of enrollment and imaging.

## Results

Only individuals fulfilling the inclusion and exclusion criteria will be considered as study subjects. This study is a registered, unfunded protocol study (CTRI/2025/06/088238) and is currently in the pre-recruitment phase. Participant enrollment and data collection are scheduled to be conducted from September 2025 to May 2027. As of the time of manuscript submission, no participants have been recruited and data analysis has not yet commenced. The primary outcome will evaluate condylar morphological changes associated with chronic areca nut (AN) chewing, while secondary outcomes will assess pathological alterations of the condyle, including osteophyte formation with subcortical sclerosis, articular surface flattening of the superior condylar surface with subcortical sclerosis, abnormal condylar shape, and surface erosion. The results are expected to provide insights into the functional impact of chronic AN chewing on the temporomandibular joint and may aid in early identification of pathological condylar changes. Study results are anticipated to be published after completion of data analysis in 2027.

## Discussion

Chronic AN chewing has been extensively associated with oral mucosal lesions. However, its impact on the TMJ, particularly on condylar morphology, remains insufficiently studied using CBCT. Almashraqi et al [6] investigated CBCT findings in the TMJ of individuals with a history of chronic qat chewing (QC). They examined TMJ dimensions and osteoarthritic alterations on CBCT. According to the qualitative CBCT results, QC had substantially more osteoarthritic alterations than non qat chewers, including osteophyte, subcortical sclerosis, articular surface flatness, and subcortical cysts. Quantitative assessments of condylar dimensions showed no significant difference among both categories. Notably, the chewing side of individuals with QC displayed more alterations than the nonchewing side. The findings show that chewing qat has negative effects on the TMJ, primarily in the form of osteoarthritic alterations [6].

Liu et al [9] performed a study to investigate the relation between severe tooth wear caused by betel nut chewing and the development of TMD. Age, sex, and severely worn dentition due to betel nut chewing were significant factors contributing to the overall occurrence of TMD. Multivariable analysis revealed a significant, dose-dependent association between intra-articular TMD and badly worn dentition resulting from betel nut chewing, indicating a direct relationship between the severity of tooth wear and the likelihood of developing intra-articular TMD [9].

Al-koshab et al [22] investigated the morphology of the condyle and glenoid fossa by using CBCT in South-East Asians. Condylar length and roof of the glenoid fossa (RGF) thickness did not differ significantly by sex; however, male participants had significantly larger condylar volume, width, height, and joint gaps. While the mean left condylar height and RGF thickness were higher, the mean right TMJ condylar volume, width, and length were significantly higher when comparing the 2 TMJs. With the exception of condylar height, which is larger in Chinese participants, we could not find any significant differences between the 2 ethnic groups’ condylar measures and RGF thickness [22].

Khalid Nawaz et al [24] conducted a clinical study on TMJ dysfunction associated with betel nut chewing and reported that long-term chewing of betel nuts can lead in TMJ dysfunction syndrome, as the masticatory forces are transferred to the TMJ. Chewing betel nuts for an extended period can result in TMJ dysfunction syndrome. The consistency of the betel nut is another important factor in TMJ dysfunction syndrome. Clicking and preauricular pain appeared to be the most common symptoms across all age groups. They concluded that the incidence in female participants was greater than that in male participants [23].

Larheim et al [25] conducted a study on TMJ diagnostics by using CBCT. This study provides an updated perspective on the role of CBCT in evaluating TMJ conditions. The study highlights the diagnostic accuracy and value of CBCT compared to other imaging methods. CBCT is a cost-effective and dose-efficient tool for assessing different TMJ issues, such as osteoarthritis, juvenile osteoarthritis, and rheumatoid arthritis. CBCT offers better images of bone structures than conventional radiographs and MRI scans [25].

## Appendix

Multimedia Appendix 1 Sample size calculation.

Multimedia Appendix 2 Data on the morphological and pathological changes of the condyle.

Multimedia Appendix 3 SPIRIT 2025 checklist.

## Abbreviations

AN: areca nut
CBCT: cone beam computed tomography
CT: computed tomography
IEC: institutional ethics committee
MRI: magnetic resonance imaging
RGF: roof of the glenoid fossa
TMD: temporomandibular disorder
TMJ: temporomandibular joint
QC: qat chewing
